### Sample size calculation

An a priori sample size calculation was conducted using G*Power software (V.3.1.9.4). The estimation was based on the Minimal Clinically Important Improvement for the COMI, considered the primary outcome measure, with a reference value of 2.6 points.^47^ This endpoint was defined as the difference in COMI scores between baseline and immediately postintervention (week 4).

The expected SD of the COMI score in both groups was conservatively estimated at 3, based on a previous study^48^ and expert clinical judgement. With a significance level (α) of 0.05 (two-tailed) and a desired statistical power of 80% (1−β), the required sample size was calculated to be 22 participants per group to detect a clinically meaningful between-group difference.

To account for an anticipated dropout rate of 10%, the recruitment target was adjusted to 24 participants per group. Therefore, a total of 48 participants will be enrolled in this trial.

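### The sample size arithmetic is right, but its inputs do not match the planned test: a within-patient improvement threshold serves as the between-arm difference, and the SD is worded as that of the score while the test is on change

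*Protocol article*

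**What the plan says.** The Sample size calculation section of the protocol article says that the estimate was "based on the Minimal Clinically Important Improvement for the COMI, considered the primary outcome measure, with a reference value of 2.6 points". Its next sentence links this to change over time: "This endpoint was defined as the difference in COMI scores between baseline and immediately postintervention (week 4"). The spread is then given as follows: "The expected SD of the COMI score in both groups was conservatively estimated at 3", with a previous study and expert clinical judgement as its sources. With a two-sided α of 0.05 and 80% power, the section arrives at 22 participants per group "to detect a clinically meaningful between-group difference". A 10% dropout allowance takes this to 24 per group, 48 in all.

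The Primary analysis section compares the change in COMI from baseline to week 4 between the arms with an independent samples t-test, or a Wilcoxon-Mann-Whitney test if normality fails. There is no baseline adjustment. Under Randomisation/blinding and Interventions, both arms follow the same exercise programme and differ only in active or sham stimulation.

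**The concern.** The planned test needs two inputs on its own scale: a difference between arms in mean change, and the SD of change. The section supplies neither in clear terms.

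- **Difference.** A minimal clinically important improvement says how far a patient must move from his or her own baseline for the move to matter. Used as the difference between arms, it requires stimulation to add a full important improvement to whatever exercise with sham achieves. The article gives no important difference between arms and no argument for equating the two quantities. Its Background describes the effect of exercise on pain as small and reports no significant pooled effect of motor-cortex stimulation on pain or disability, so it offers no support for an added effect of this size.
- **SD.** The SD of a score and the SD of its change are different quantities, linked by the correlation between the two visits. That correlation is not stated.

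This is the only confirmatory outcome, since the Secondary analysis section makes the others exploratory. The sample size paragraph therefore determines what a null result can be said to show. Taken at its word, a non-significant result would suggest, with 80% power, that no clinically meaningful benefit was missed.

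**Working it through.** **Inputs from the protocol:** difference δ = 2.6; SD = 3; two-sided α = 0.05; n = 22 per arm; 1:1 allocation; t-test on change.

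**Assumed, because the protocol gives no figure:** the baseline to week-4 correlation ρ; equal SDs at both visits; true differences smaller than 2.6, as illustrations.

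**1. The plan's own figure.** Standardised difference = 2.6/3 = 0.867. Standard error = 3 × √(2/22) = 0.905. Noncentrality = 2.6/0.905 = 2.87 on 42 degrees of freedom. Exact power from the noncentral t distribution is 80.2% with 22 per arm and 78.2% with 21. The stated 22 is reproduced.

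**2. Smaller added benefits, taking 3 as the SD of change** (22 per arm):

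| True difference between arms | Power | n per arm for 80% |
|---|---|---|
| 2.6 | 80% | 22 |
| 2.0 | 58% | 37 |
| 1.5 | 37% | 64 |
| 1.3 (half the threshold) | 29% | 85 |
| 1.0 | 19% | 143 |

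**3. If 3 is the SD of the raw score.** SD of change = 3 × √(2(1 − ρ)). For example, at ρ = 0.3 it is 3 × √1.4 = 3.55. Power for δ = 2.6 with the unadjusted t-test, 22 per arm:

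| ρ | SD of change | Power | n per arm for 80% |
|---|---|---|---|
| 0 | 4.24 | 51% | 43 |
| 0.3 | 3.55 | 66% | 31 |
| 0.4 | 3.29 | 73% | 27 |
| 0.5 | 3.00 | 80% | 22 |
| 0.6 | 2.68 | 88% | 18 |
| 0.7 | 2.32 | 95% | 14 |

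The two SDs coincide only at ρ = 0.5. Below that value the plan falls short of 80%; above it the plan has power to spare.

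**4. With adjustment for baseline.** The residual SD is 3 × √(1 − ρ²), which cannot exceed 3. With 22 per arm and one degree of freedom spent on the covariate (41 left), power for 2.6 is 80.1% at ρ = 0 (residual SD 3.00), 84% at ρ = 0.3 (2.86) and 90% at ρ = 0.5 (2.60). A score SD of 3 is then a valid input, and the 80% holds for any ρ of 0 or more.

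**5. Precision.** The expected 95% confidence interval half-width for the unadjusted test is 2.018 × SD of change × √(2/22). It is 1.8 points if the SD of change is 3. On the raw-score reading it is 2.3 at ρ = 0.2 and 1.4 at ρ = 0.7. The 1.8 therefore belongs to one reading and is not a property of the design.

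**The case against.** The strongest reply is that nothing has been miscalculated, and that is correct: 2.6, 3 and 22 fit together. The SD sentence also directly follows the one that defines the endpoint as a change, so 3 may well be meant as the SD of that change. On that reading the calculation agrees with the t-test. The previous study cited for the SD might settle this, but it is not at hand.

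A reader might go further and infer that the trial is underpowered for its own target, or that the 80% is wrong. The protocol does not support that. If 3 is the SD of change, power for 2.6 is 80.2%; if it is the SD of the score, power may lie on either side of 80%, and it exceeds 80% once ρ is above 0.5.

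It can also be said that the article nowhere promises to read a null result as evidence of no benefit, and that power at smaller differences is often left to other documents. That is fair, and the absence of such figures is not the point here. What remains is what the section itself asserts: it calls an improvement threshold a clinically meaningful difference between groups, and it calls conservative an SD whose scale is unclear. The concession about the arithmetic touches neither statement.

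**Conclusion.** The point holds as a mismatch between the inputs and the planned test, not as an error of calculation.

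- **The difference is mislabelled.** This does not depend on how the SD is read. The 80% applies to an added benefit as large as a whole within-patient important improvement. With an SD of change of 3, an added benefit of 2.0 points would be detected 58% of the time and one of 1.3 points 29% of the time. Those two values are illustrations; the protocol names no smaller difference of interest.
- **The scale of the SD is unclear.** If it is the raw-score SD, with equal SDs at both visits, power for 2.6 runs from 51% at ρ = 0 to 95% at ρ = 0.7. The claim that the SD is conservative is thus unproven in either direction.

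The plan should be corrected on both counts. The number of patients need not change.

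**What to change.** Keep 24 per arm.

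1. **Primary analysis section.** Preferably, amend it so that week-4 COMI, or its change, is compared between arms with adjustment for baseline COMI, which is already collected. A score SD of 3 then gives at least 80% power for 2.6 with 22 per arm at any ρ of 0 or more. If the unadjusted t-test is kept, state the SD of change assumed and restate the power for it. Power should not be quoted for an adjusted analysis unless that analysis becomes the planned one.
2. **Sample size calculation section.** Say which SD the 3 is. Describe 2.6 as a within-patient improvement threshold adopted as the target between arms, and remove the claim that it is an established clinically meaningful difference between groups.
3. **Interpretation.** State that a non-significant result will be read from its confidence interval.

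Cost: a short amendment to the primary analysis and a reworded paragraph, with no extra patients. The Timeline and feasibility section expects recruitment to end in February 2026, and this version is dated 12 February 2026, so the change should be dated and filed before anyone sees outcome data by arm. If the unadjusted test is kept, the restated power may be lower or higher than 80%.

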### Statistical analysis

All primary and secondary outcome measures will be analysed according to the intention-to-treat principle. A two-tailed superiority testing approach will be applied, with the level of statistical significance set at α=0.05 (p<0.05).

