#### Primary analysis

To evaluate between-group differences in the primary outcome, the change in COMI score from baseline to immediately postintervention (week 4), an independent samples t-test will be used, provided the data meet the assumption of normality. If the assumption of normality is violated, as determined by appropriate normality tests (eg, Shapiro-Wilk), a non-parametric alternative, the Wilcoxon-Mann-Whitney U test, will be employed to assess the statistical significance of the observed differences.

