#### Clinical outcomes

The longitudinal evolution of each secondary outcome (COMI, ODI, VAS, HADS, FABQ, PCS) at weeks 4, 12 and 24 will be compared between groups using a mixed-effects regression model.

A random effect for subjects and fixed effects for time and group will be included in the model. To assess potential differences in outcome trajectories between groups over time, an interaction term between time and group will be specified and evaluated using a likelihood ratio test. Intention-to-treat approach will be applied.

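### The primary test on COMI change can use only participants with a week-4 score unless values are imputed, which sits badly with the intention-to-treat statement; the mixed model already planned for COMI is the better primary analysis

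*Protocol article*

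**What the plan says.** - **Population.** The opening of the Statistical analysis section says: "All primary and secondary outcome measures will be analysed according to the intention-to-treat principle".
- **Primary test.** The Primary analysis section says that for "the change in COMI score from baseline to immediately postintervention (week 4), an independent samples t-test will be used". If normality is rejected, "a non-parametric alternative, the Wilcoxon-Mann-Whitney U test, will be employed". Neither test adjusts for baseline beyond taking the difference.
- **Sample size.** The Sample size calculation takes the COMI improvement threshold "with a reference value of 2.6 points" and an SD of 3. It states "a desired statistical power of 80% (1−β), the required sample size was calculated to be 22 participants per group", and then: "To account for an anticipated dropout rate of 10%, the recruitment target was adjusted to 24 participants per group".
- **Second use of week-4 COMI.** The Secondary outcomes section lists COMI again, with week 4 among its time points. Under Secondary analysis, Clinical outcomes, COMI and the other scales "at weeks 4, 12 and 24 will be compared between groups using a mixed-effects regression model". That model has a random subject effect, fixed effects for time and group, and a likelihood ratio test of their interaction.
- **Ranking.** The Secondary analysis section draws the main conclusions from the primary analysis and treats secondary outcomes as exploratory.

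**The concern.** A change score needs both the baseline and the week-4 value. Without imputation, the test that carries the trial's conclusions is therefore run on participants observed at week 4, while the same section promises intention-to-treat. The protocol anticipates 10% dropout, so the case will probably arise.

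The protocol also plans a method for COMI that copes better with partial follow-up, but gives it only an exploratory role. A participant who misses week 4 and returns at week 12 or 24 contributes to the mixed model and not to the t-test.

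Three things are at stake:
- precision in a trial of 48 people;
- clarity about who is in the confirmatory comparison;
- the prospect of two COMI results that do not agree.

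**Working it through.** **1. Reproducing the planned size.** Inputs from the Sample size calculation: difference 2.6, SD 3, two-sided α 0.05, power 80%. The Randomisation section gives 1:1 allocation. The standardised difference is d = 2.6/3 = 0.867. The noncentral t calculation gives n = 21.90, so 22 per group (power 80.2%). The stated figure reproduces.

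**2. Power of the t-test after the planned loss.** 24 × 0.90 = 21.6 per group with a week-4 value.

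| Analysed per group | Power of t-test |
|---|---|
| 24 (no loss) | 83.6% |
| 21.6 (10% loss, as planned) | 79.4% |
| 19.2 (20% loss, assumed) | 74.3% |

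At 10% the loss of power is small. Sample size is not the problem.

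**3. What baseline adjustment adds.** Assume that the SD of 3 is the SD of change, that the variance σ² is equal at baseline and week 4, and that the correlation between the two is ρ. The protocol gives no ρ, so a range is shown.
- Variance of change: 2σ²(1 − ρ) = 9, so σ² = 9/[2(1 − ρ)].
- Residual variance after adjustment: σ²(1 − ρ²) = 9(1 + ρ)/2.
- Residual SD: 3 × √[(1 + ρ)/2].

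| ρ (assumed) | Residual SD | d = 2.6/SD | Power at 21.6 per group |
|---|---|---|---|
| 0.3 | 2.42 | 1.07 | about 93% |
| 0.5 | 2.60 | 1.00 | about 89% |
| 0.7 | 2.77 | 0.94 | about 85% |
| Unadjusted change | 3.00 | 0.867 | 79% |

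This is the gain from adjustment alone, computed on participants seen at week 4. Those who return later would add a little.

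**4. Can the two COMI analyses disagree?** Complete data were simulated for 24 per group with change SD 3 and 2,000 runs per setting. A common correlation of 0.3, 0.5 or 0.7 between visits was assumed. With a 2.6-point effect at week 4, sustained or not, the t-test and the interaction test differed on significance in about 11–13% of runs. With no effect they differed in about 7%. They are different tests, so some discordance is expected even without missing data.

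**5. Size of a possible dropout bias (illustration only).** Bias in one arm's mean = share lost × difference in improvement between those seen and those lost. Assume that active-arm dropouts improve 3 points less and that the other arm has no such gap:
- 10% loss: 0.10 × 3 = 0.30 points; 0.30/2.6 = 12% of the target difference.
- 20% loss: 0.20 × 3 = 0.60 points; 0.60/2.6 = 23%.

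**6. Does the mixed model remove that bias?** The 10% scenario was simulated with no data after baseline for dropouts (SD 3, correlation 0.5, 3,000 per arm, all assumed). The effect in all randomised was −2.28. The t-test on observed change gave −2.56 and the common-baseline mixed model gave −2.55. The bias is essentially unchanged, because missingness here depends on the unseen value.

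**The case against.** **The exclusion is inferred.** A reader might conclude that the protocol drops everyone without a week-4 COMI and so contradicts its intention-to-treat statement. The text does not go that far. Intention-to-treat also means analysis as randomised, imputation before a t-test would fit both statements, and a missing-data rule may stand in an analysis plan that is not shown. This stands.

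**The dropout allowance proves nothing.** Raising 22 to 24 is ordinary practice and does not by itself show a completer analysis. This stands.

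**Stopping sessions is not the same as missing data.** COMI is completed online by the participant, so someone who leaves the programme can still give a week-4 score. This stands and makes the bias figures less certain.

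**The two COMI analyses do not conflict.** A reader might see two rival answers to one question. The protocol ranks them, and the planned likelihood ratio test concerns trajectories over time, not the week-4 contrast alone. What remains is duplication of week-4 COMI as primary and secondary.

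**The model does not cure informative dropout.** Step 6 of the working confirms this. The case for the model must rest on precision and on participants who return later. Bias needs a separate sensitivity analysis, which could equally accompany a t-test.

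**The change is late.** Recruitment began in August 2023 and was due to end in February 2026, and amendments go to the ethics committee and the registry. That is a real cost, but not a reason against a change made before unblinding.

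**Conclusion.** The point holds in a limited form. As fixed, the primary test uses only participants with a week-4 COMI unless values are imputed, and this fits poorly with the intention-to-treat statement. Week-4 COMI is analysed twice, with the ranking already settled.

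The main benefit of changing is precision: power of about 85–93% against 79% at 10% loss. This assumes correlations from 0.7 down to 0.3, a change SD of 3 and equal variances. A smaller benefit is the use of participants who miss week 4 but return.

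The 0.3 and 0.6 point biases are illustrations, not estimates. They assume a 3-point gap confined to one arm, and similar dropout in both arms would bring the between-group bias near zero. Even in that scenario, 0.30 points is about one third of the standard error of the difference, 3 × √(2/22) = 0.90. The change is worth making, but the planned analysis is not invalid.

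**What to change.** 1. Make the week-4 group contrast from the COMI mixed model the single primary analysis. Use baseline adjustment, categorical time, and all randomised participants with available data, analysed as randomised. It replaces both the t-test and the switch to Mann-Whitney after a normality test.
2. List COMI as a secondary outcome for weeks 12 and 24 only.
3. Add one sensitivity analysis that applies an unfavourable shift to missing week-4 values, with the shift fixed in advance.
4. State in the protocol that the sample size was computed for a t-test on change and is kept. Under the assumptions shown, the adjusted analysis needs no more participants.

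**Cost.** No new data are needed, and a mixed model for COMI is already planned. The model relies on missing-at-random, which the sensitivity analysis probes but cannot verify. The change needs a protocol amendment, ethics submission and a registry update, all before unblinding.

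If the t-test is kept, the least that is needed is a statement of how a missing week-4 COMI enters it, together with items 2 and 3.

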#### Primary analysis

To evaluate between-group differences in the primary outcome, the change in COMI score from baseline to immediately postintervention (week 4), an independent samples t-test will be used, provided the data meet the assumption of normality. If the assumption of normality is violated, as determined by appropriate normality tests (eg, Shapiro-Wilk), a non-parametric alternative, the Wilcoxon-Mann-Whitney U test, will be employed to assess the statistical significance of the observed differences.

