#### Primary outcome

The primary outcome will be the mean difference in the multidimensional impact of CLBP, as measured by the Core Outcome Measures Index (COMI), between baseline and immediately postintervention (week 4).

The COMI consists of seven items assessing five dimensions: pain, function, symptoms-specific well-being, quality of life and disability. COMI is reliable and has been validated in French.^43^ Scores range from 0 (excellent health status) to 10 (worst health status).

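### The primary COMI comparison is an unadjusted t-test on change that a normality test can swap for a rank test; one fixed baseline-adjusted ANCOVA would be more precise and fully prespecified

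*Protocol article*

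**What the plan says.** Under Primary analysis, the between-group comparison of the change in COMI has two stages. First, "an independent samples t-test will be used, provided the data meet the assumption of normality". If normality fails, as judged by suitable tests with Shapiro-Wilk given as an example, "a non-parametric alternative, the Wilcoxon-Mann-Whitney U test, will be employed to assess the statistical significance of the observed differences". No baseline covariate is named. The normality test, its level, and whether it is run per arm or on pooled residuals are not fixed.

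Three other places bear on this:

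- Primary outcome: "The primary outcome will be the mean difference in the multidimensional impact of CLBP", from baseline to week 4.
- Sample size calculation: 2.6 COMI points, SD 3, two-sided alpha 0.05, 80% power, giving 22 per group (24 after dropout).
- Secondary analysis: the main conclusions come from the primary analysis, and secondary outcomes are exploratory. The mixed model under Clinical outcomes also covers COMI at week 4, but it belongs to this exploratory tier.

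**The concern.** There are two separate weaknesses.

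**Use of baseline.** A change score fixes the slope of week-4 COMI on baseline at 1. If the true slope is lower, the change score over-corrects for any baseline difference between arms and has a larger variance than ANCOVA, which estimates the slope. COMI is scheduled at baseline for everyone, so the lost precision could be recovered without new data. Randomisation is by permuted blocks with no stratification described, and there are 24 per arm, so nothing in the design or the primary analysis deals with chance imbalance in baseline COMI.

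**Choice of test.** Which hypothesis the primary p-value addresses is settled by the outcome data. The t-test compares means. The rank test asks whether values in one arm tend to exceed those in the other, and by itself gives no difference in COMI points to set against 2.6. Because the gate is only loosely specified, two analysts could follow the text and run different primary tests.

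**Working it through.** **Inputs from the protocol:** difference 2.6, SD 3, two-sided alpha 0.05, power 80%, 22 per arm analysed, 24 per arm randomised. **Assumed:** the baseline to week-4 correlation rho (not given; 0.3 to 0.7 shown), equal variances at the two visits, and the distribution shapes in step 5.

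**1. The protocol's own figure.** d = 2.6/3 = 0.867. The noncentral t gives 21.9 per group, so 22, with power 80.2% at 22. The stated 22 per group is reproduced for the unadjusted t-test.

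**2. Variance of ANCOVA against change score.**

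- Change: s0² + s1² − 2·rho·s0·s1
- ANCOVA: s1²(1 − rho²)
- Change minus ANCOVA: (s0 − rho·s1)², which is never negative and is zero only when the slope rho·s1/s0 equals 1.

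With s0 = s1 the ratio ANCOVA/change is (1 − rho²)/[2(1 − rho)] = (1 + rho)/2, that is 0.65, 0.75 and 0.85 at rho 0.3, 0.5 and 0.7.

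**3. Power for 2.6 points at 22 per arm** (noncentral t, one degree of freedom lost for ANCOVA). The sample-size section attaches the SD of 3 to the COMI score but defines the endpoint as a change, so both readings are shown.

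| rho | SD of change = 3: t-test | ANCOVA | SD of score = 3: t-test | ANCOVA |
|---|---|---|---|---|
| 0.3 | 80% | 94% (residual SD 2.42) | 66% (SD of change 3.55) | 84% (2.86) |
| 0.5 | 80% | 90% (2.60) | 80% (3.00) | 90% (2.60) |
| 0.7 | 80% | 86% (2.77) | 95% (2.32) | 98% (2.14) |

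**4. Chance imbalance.** With a baseline SD of 3 and 24 per arm, one standard error of the baseline difference is 3·√(2/24) = 0.87 points. Given such an imbalance, the change-score difference shifts by (1 − rho)·0.87. At rho 0.5 this is 0.43 points, or 0.43/2.6 = 17% of the target.

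**5. The normality gate.** Simulated with 22 per arm and 8,000 runs: Shapiro-Wilk at 0.05 in each arm, then t-test or Mann-Whitney. Shapes are standardised, and the planned effect is a shift of 0.867 SD.

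| Shape in both arms | Switches to rank test (no effect) | Two-stage type I error | The two tests disagree on significance at the planned effect |
|---|---|---|---|
| Normal | 10% | 5.5% | 5.4% |
| t, 5 df | 37% | 4.4% | 8.8% |
| Lognormal, sigma 0.5 | 81% | 5.4% | 11.3% |
| Exponential | 99% | 4.9% | 14.6% |

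The Monte Carlo standard error near 5% is √(0.05·0.95/8000) = 0.24 percentage points. If pooled residuals are tested instead, exactly normal data switch in about 5% of trials.

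With equal means but a normal shape in one arm and an exponential shape in the other, the gate switches in 88% of trials. The two-stage rule then rejects in 7.6%, against 5.1% for the t-test alone. A second run gave 8.0% against 5.4%.

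**The case against.** The strongest case for the plan is that its default test is sound. A t-test on change is unbiased under randomisation, holds its type I error, matches the stated endpoint and matches the sample-size method. This stands. A reader might infer that baseline COMI is thrown away or that the estimate is biased. The protocol supports neither reading: baseline is subtracted, and the shift in step 4 is conditional on an imbalance that has occurred. An imbalance of at least one standard error arises in about 32% of trials. The baseline SD may also be below 3, since the protocol calls that value conservative and entry requires pain of at least 3 out of 10.

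The size of the ANCOVA gain rests on a correlation the protocol does not give, and the (1 + rho)/2 ratio needs equal variances. If week-4 scores vary more than baseline scores, the slope moves towards 1 and the gain shrinks. If 3 is the score SD and rho is 0.7, the gain is only 95% to 98%. This also stands, which is why a range is shown.

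A reader might further infer that the gate seriously inflates false positives. It does not when the arms share a shape (4.4% to 5.5%). The gate costs almost no power with normal data (79.7% against 79.9% for the t-test) and gains power with skewed data. When only the shapes differ, the treatment has changed the distribution, so a rank-test rejection is not plainly false. It is still a rejection when the means are equal, and the mean difference is the stated target.

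Finally, the rank test is named only for significance, so a mean difference could still be reported and the target quantity is not unknown. But the estimate and the p-value would then address different hypotheses. The mixed model gives an estimate on the COMI scale, but it is exploratory and does not replace the primary test.

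**Conclusion.** The point holds as one of efficiency and prespecification, not of validity. Under equal variances, baseline adjustment would cut the variance by 35% to 15% for rho 0.3 to 0.7. If 3 is the SD of change, power rises from 80% to between 94% and 86%. If 3 is the score SD, the gain runs from 66% to 84% at rho 0.3 down to 95% to 98% at rho 0.7. The gate makes the primary hypothesis depend on the outcome data, and at the planned effect the two tests disagree on significance in 5% to 15% of trials under the shapes tried. Type I error is close to nominal with a common shape, and about 8% against about 5% in the normal versus exponential example with equal means. These figures rest on assumed correlations and shapes. It should be fixed, and it is a free improvement in patients and data. The documents do not support calling the primary analysis invalid.

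**What to change.** Before unblinding, replace the Primary analysis text with one method: ANCOVA of week-4 COMI on arm and baseline COMI, reporting the adjusted mean difference with its 95% CI and two-sided p-value. Regressing the change on arm and baseline gives the same treatment coefficient, so the endpoint can still be described as change. Delete the normality pre-test. Keep the Wilcoxon-Mann-Whitney test, or a permutation test, as a sensitivity analysis only.

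Arm plus baseline fits the protocol's own limit of one predictor per ten participants (48/10 allows four). No extra patients or measurements are needed. The cost is wording, plus the ethics submission and registry update that the protocol requires for amendments. Timing matters: recruitment was expected to finish in February 2026, the month of this protocol version, and a change made after unblinding would not be credible.
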